## BACKGROUND AND SIGNIFICANCE

### Historical background

Hospitals are the standard of care for acute illness in the US, but hospital care is expensive and often unsafe, particularly for older individuals. While admitted, 20% of older adults suffer delirium, over 5% contract hospital-acquired infections, and most lose functional status that is never regained. Timely access to inpatient care is poor: many hospital wards are typically over 100% capacity, and emergency department waits can be protracted. Moreover, hospital care is increasingly costly: many internal medicine admissions have a negative margin (i.e., expenditures exceed hospital revenues) and incur patient debt.

### The home hospital model and prior clinical studies

The home hospital model of care provides in-home acute care to acutely ill patients who would normally be admitted to a traditional hospital. This sort of substitutive care has been provided around the world for decades. Earlier studies of home hospital care in Australia, Italy, Spain, and elsewhere demonstrated lower costs, while either maintaining or improving on quality, safety, and patient experience. In the United States, 2 principle studies of the home hospital model have demonstrated that a sizeable proportion of acute care can be delivered in the home with equal quality and safety, 20% reduced cost, and 20% improved patient experience.

In late 2016, we launched a randomized controlled trial (RCT) of home hospital care, the first RCT to be performed in the US context. We first performed a small pilot with 21 patients. In short, we found the same as our international colleagues: cost savings while maintaining safety, quality, and patient experience.

In July, 2017, we amended our protocol and relaunched the RCT at Brigham and Women's Hospital (BWH) and Brigham and Women's Faulkner Hospital (BWFH) with several key improvements. We added to our catchment zone (5-miles around both BWH and BWFH, not just BWH), removed certain exclusions (eg dementia), and added certain conditions (eg gout exacerbation). We subsequently enrolled 91 patients and published our findings, which corroborated prior work: lower cost, lower utilization, and improved physical activity. No large changes in quality or safety were observed, although the study was not powered to closely scrutinize these data.

### Rationale

Our encouraging outcomes, coupled with the hospital's ongoing capacity concerns, led the hospital to require a single-arm intervention-only home hospital study for our current slate of included conditions that began in January, 2018. We have enrolled over 300 patients since January, 2018 very successfully and have consistently presented our safety data for the Committee's review. With our present local

data, compounded by the plethora of international studies cited above, we believe we have shown that home hospitalization delivers a reasonable substitute to hospitalization for correctly selected patients.

We seek to continue and expand this work in the context of IRB approval for several reasons, including the continued ability to

- employ devices in off-label uses. For example, the IRB previously approved the use of a wireless patch to record and report on vital signs. We continue to benefit from use of this device. We seek to deploy additional technologies to the home, all described below.
- deploy novel personnel. For example, the IRB previously approved the use of paramedics in our home hospital team. We intend to continue our use of paramedics, described below, and test in a retrospective pre/post design the impact of our already-deployed home hospital paramedic on safety and patient experience.
- Prospectively collect and report on a battery of outcomes, many of which are first-in-class and will benefit from additional sample size. For example, the IRB previously approved collection of daily steps.
- Test remote physician care. In a randomized controlled non-inferiority trial, we will test an in-person daily physician visit (“in-person care;” control) vs a daily physician visit conducted remotely via video facilitated by a care team member (“remote care;” intervention) for patients who are home hospitalized. For patients in the remote care arm, the physician can pragmatically choose to see a patient in-person based on the clinical context.

Of importance, we have chosen to add 3 diagnoses (acute pancreatitis, inflammatory bowel disease exacerbation, and cystic fibrosis exacerbation) to this protocol that were originally planned to be randomized in our randomized controlled protocol (2016P001337). Due to volume constraints (high volumes of current diagnoses coupled with no budgeted ability to expand staff) we have not been able to start to care for these 3 new diagnoses but have carefully noted that we would be unlikely to enroll sufficient patients to make a RCT meaningful for these new diagnoses. We do now have the ability to hire additional staff members, allowing us to expand to these new diagnoses. We still believe that home hospital care could benefit these patients and want the opportunity to care for them. We will continue to closely vet each case for any safety issues and have any issues reviewed by our safety review committee as per our current protocol. With the IRB’s approval, we will therefore move these diagnoses to the present protocol. We will continue to maintain protocol 2016P0001337 for bariatric surgery, as we are confident we can enroll a sufficient volume.

## SPECIFIC AIMS

### *Primary Aim*

We will accomplish a 20% reduction in hospitalization cost for selected hospitalized adults who would normally have been admitted to the hospital.

### *Secondary Aims*

We will accomplish the following for the above-mentioned selected hospitalized adults:

- reduce health care utilization;
  - For example: decreased length of stay, number of labs/imaging, readmissions, ED visits
- maintain or improve on patient safety;
  - For example: reduced risk of delirium, falls
- maintain or improve on quality of care;
  - For example, high-value: increase in appropriate antibiotic selection, hours of sleep

- For example, low-value: decrease in use of urinary catheter, inappropriate medications in the elderly
- maintain or improve on functional status and quality of life; and
  - For example: increase in EuroQol-5D-5L, activities of daily living scale
- improve absolute patient experience by 20%.
  - For example: increase in 3-item care transition measure, PROMIS experience measures

***Please refer to our performance measures below for more details regarding the definitions and sources for each of these measures.***

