### Study endpoints

| Study                                 | Type                                                                         | Primary                    | Secondary                                                                                                         |
|---------------------------------------|------------------------------------------------------------------------------|----------------------------|-------------------------------------------------------------------------------------------------------------------|
| Home hospital vs traditional hospital | Prospective intervention group, retrospective propensity-weighted evaluation | Cost of acute care episode | Cost of acute care episode and 30 days post-discharge
Length of stay
Unplanned readmission after index, y/n |

|                                                         |                                                                              |                                                       |                                                                                                                                   |
|---------------------------------------------------------|------------------------------------------------------------------------------|-------------------------------------------------------|-----------------------------------------------------------------------------------------------------------------------------------|
|                                                         |                                                                              |                                                       | Number of adverse events
Picker experience questionnaire                                                                       |
| Remote vs in-person home hospital physician             | RCT, non-inferiority                                                         | Number of adverse events                              | Unplanned readmission after index, y/n
Picker experience questionnaire
Global experience score                              |
| Early transfer to home hospital vs traditional hospital | Prospective intervention group, retrospective propensity-weighted evaluation | Cost of acute care episode and 30 days post-discharge | Unplanned readmission after index, y/n
Picker experience questionnaire
Global experience score
Number of adverse events* |

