| Paramedic + nurse care vs nurse care alone              | Retrospective, non-inferiority, propensity-weighted evaluation               | Number of adverse events                              | Unplanned readmission after index, y/n
Picker experience questionnaire
Global experience score
Personnel costs           |

\*Non-inferiority for this outcome

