## Statistical methods

### *Home hospital vs traditional hospital*

#### *Quantitative*

We plan to form 3 different control groups (with groups listed in order of preference):

1. Patients who were deemed eligible for home hospital, but the service was full (and they were not enrolled subsequently if the service was no longer full);
2. Patients who were deemed eligible for home hospital, but lived outside of the 7.5-mile catchment area; and
3. Patients who were admitted to the hospital.

For each control group, we will use propensity score weighting, adjusting for covariates of interest (see table above), baseline functional status, and DRG. We will be cognizant of over-adjustment depending on our final sample size for each group above. If possible, we will use only group 1 above, as it is the strongest. If we have insufficient control group sample size, we may choose to combine groups 1 and 2 above.

The primary outcome (hospitalization cost) will be assessed using a generalized linear model assuming a gamma distribution with a log link. We will use a multivariable regression approach for secondary

outcomes, using logistic regression for binary outcomes and non-transformed linear regression for normally distributed continuous outcomes as appropriate.

We *a priori* plan to perform a subgroup analysis that does not involve any outlier participants, should this occur. We also *a priori* plan subgroup analyses by diagnosis, by age group, by disposition, by location of admission (e.g., ED, floor, clinic, and home), and by daily activity level. We also *a priori* plan to analyze our outcomes with means, but also with median and interquartile ranges, which are less subject to outlier effects. We may choose to employ non-parametric tests of significance should our data be nonparametric.

We *a priori* plan to adjust our secondary analyses using the Benjamini-Hochberg method. We *a priori* choose a false-discovery rate of 0.20.

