## Power analysis

### *Standard Home Hospitalization*

Our recent RCT data suggest that at 90% power, we will require 38 patients in each arm. However, we also have prespecified a smallest important difference of \$1000, for which we will need 144 patients in each arm at 90% power.

For 30-day readmission, we will require 110 patients in each arm at 90% power (23% vs 7%). If the effect size is indeed smaller, for example 23% vs 15%, we will need 528 patients in each arm. However, we will not be able to power around a smallest important difference of 3%, for which we would need 4006 patients in each arm.

For percentage with a safety event, we will require 641 patients in each arm at 90% power and 493 patients in each arm at 80% power (15% vs 9%).

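### In home versus traditional hospital, the aim to maintain safety has no margin and no non-inferiority test, so the planned difference test cannot by itself support it

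*Protocol*

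**What the plan says.** - **Aim.** Under Secondary Aims the protocol undertakes to "maintain or improve on patient safety".
- **Endpoint.** The Study endpoints table describes home versus traditional hospital as "Prospective intervention group, retrospective propensity-weighted evaluation". Cost is primary, and the number of adverse events is one of five secondary outcomes, with no non-inferiority label.
- **Same outcome elsewhere.** The remote-care and paramedic rows are non-inferiority by design type, with adverse events as primary outcome. In the early-transfer row adverse events carry an asterisk, explained as "Non-inferiority for this outcome". Early transfer is also compared with traditional hospital, and its methods section adopts the analysis of the main comparison.
- **Analysis.** Statistical methods, Quantitative, plans multivariable models for the secondary measures, described as "outcomes, using logistic regression for binary outcomes and non-transformed linear regression for normally distributed continuous outcomes as appropriate". Secondary results are adjusted by Benjamini-Hochberg at a false-discovery rate of 0.20. No margin appears.
- **Size.** Power analysis, Standard Home Hospitalization, gives 38 per arm for cost, then a $1000 difference, "for which we will need 144 patients in each arm at 90% power". It gives separate sizes for readmission. For safety it says "For percentage with a safety event, we will require 641 patients in each arm at 90% power", or 493 at 80%, for 15% versus 9%. It does not say which size the comparison will use.

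**The concern.** A test for a difference can support the improve half of the aim. It cannot support the maintain half, because failing to find a difference is not evidence that a relevant excess has been ruled out. A smaller or more heavily weighted control group makes a null result more likely without making it more reassuring. The statement at stake is that acute care moved into the home is as safe as hospital care. As the protocol stands, nothing says what result would establish it.

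This goes beyond detail left to an analysis plan. The protocol itself assigns design types and non-inferiority labels row by row, and the row tied to this aim has none.

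**Working it through.** **1. What the stated safety sizes are for.** Inputs from the Power analysis: 15% and 9%, so d = 0.06 and the mean proportion is 0.12. Alpha is not stated there; two-sided 0.05 is assumed.

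n = [1.96·√(2·0.12·0.88) + z(power)·√(0.09·0.91 + 0.15·0.85)]² / 0.06²

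- 80% power: (0.9007 + 0.3851)² / 0.0036 = 459.3, so 460.
- 90% power: (0.9007 + 0.5864)² / 0.0036 = 614.4, so 615.

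Continuity correction: n′ = (n/4)·[1 + √(1 + 4/(n·d))]² gives 493 (stated 493) and 648 (stated 641, about 1% away). One-sided versions give 395 and 534 with the correction, 362 and 501 without, and do not match. The stated sizes are therefore for a two-sided test of a difference.

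**2. Chance of missing 9% versus 15%.** The contrast is turned round so that home is worse. At n = 144 per arm:

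- null SE = √(2·0.12·0.88/144) = 0.0383
- alternative SE = √((0.0819 + 0.1275)/144) = 0.0381
- power = Φ[(0.06 − 1.96·0.0383)/0.0381] = Φ(−0.395) = 0.35, so the miss is 65%.

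| Per arm | 38 | 144 | 300 | 493 | 641 |
|---|---|---|---|---|---|
| Missed, two-sided 5% | 88% | 65% | 38% | 17% | 9% |

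With five secondary outcomes and a false-discovery rate of 0.20, the Benjamini-Hochberg thresholds run from 0.20·1/5 = 0.04 to 0.20·5/5 = 0.20. At 144 per arm the miss then runs from 69% to 39%.

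The only adverse-event difference that the protocol calls clinically meaningful is 0.1 events per patient (0.09 to 0.19), stated for remote care. At 144 per arm it would be missed 31% of the time as proportions, 38% as Poisson counts, and 17% as means with the stated SD of 0.29.

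**3. What an interval could exclude at 144 per arm.** Half-width = 1.96·√(2p(1−p)/144): 6.6 points at p = 9% and 8.2 points at p = 15%. Even with an observed difference of zero, a 6-point worsening would lie inside the interval.

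**4. Sizes for a non-inferiority test.** One-sided 0.025, equal true rates, per arm at 80% / 90% power:

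| Margin | Rate 9% | Rate 15% |
|---|---|---|
| 6 points | 358 / 479 | 556 / 745 |
| 10 points | 129 / 173 | 201 / 268 |

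**5. Is 0.1 events a usable margin?** The early-transfer power statement (324 per arm, 81% power, baseline 0.15) gives no margin, but one can be backed out with Poisson variance: (1.96 + 0.878)·√(2·0.15/324) = 0.086. With the design effect 1 + 64·0.01 = 1.64 it becomes 0.086·√1.64 = 0.111. A limit near 0.1 fits that row.

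It is a loose limit, however. If the true rates were 9% in hospital and 15% at home, requiring the upper limit to be below 0.1 would accept safety with probability Φ[(0.10 − 0.06)/0.0381 − 1.96] = 18% at 144 per arm and 33% at 300.

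**6. The count itself.** The adverse-event list includes transfer back to hospital, which the Safety data table collects in the intervention arm only. The appendix shows 5 such transfers in 203 home patients, or 5/203 = 0.025 events per patient. If the same list is used here, that is a quarter of a 0.1 margin, charged to one group only.

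No figure above allows for propensity weighting or clustering, which would generally reduce precision.

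**The case against.** Several stronger readings are tempting, and the protocol does not support them.

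- *The comparison will be run at the cost sizes.* Nothing says so. Sizes for cost, readmission and safety are listed side by side and none is chosen. Over 300 home patients had already been enrolled, though the number of controls is unknown.
- *The plan misses its own relevant harm two times in three.* The 15% versus 9% contrast is a planning difference that the protocol never labels a harm; reversing it is this review's assumption. The 65% also needs 144 per arm and a two-sided 5% test, which is not the planned multiplicity rule.
- *A non-significant result will be reported as maintained safety.* That is an inference. The regression will yield an estimate and an interval, and no decision rule is given either way. In describing the earlier 91-patient trial, the Background reports no large safety changes but adds that the study was not powered to examine them closely.

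It can also be said that this is one secondary outcome of a non-randomised comparison whose primary outcome is cost, and that 0.1 events was set for a comparison in which both groups are at home. Both are fair. They limit the weight of the point and the choice of margin. They do not supply the missing criterion for maintained.

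**Conclusion.** The point holds as a mismatch between aim and analysis. The aim contains a no-worse-than claim. The planned analysis and the only safety sizing for this comparison address a difference, and no margin is set. The same outcome is non-inferiority in the three other comparisons, one of which shares the comparator and the methods.

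The size of the problem depends on a sample size that the protocol leaves open. For 9% versus 15% at two-sided 5%, the miss is about 65% at 144 per arm, 38% at 300 and 17% at 493; at 144 under the planned false-discovery rate it is 39% to 69%. These figures assume equal groups, a binary event and no loss of precision from weighting. The conclusion that the planned test cannot by itself support maintained safety does not depend on which figure applies. It is worth correcting because it governs what may be claimed about safety, but it does not touch the primary cost analysis.

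**What to change.** 1. In the Study endpoints table and in Statistical methods, mark the number of adverse events in home versus traditional hospital as non-inferiority, as is done for early transfer.
2. State and justify one margin for this comparison in advance. The 0.1 events per patient stated for remote care, which is consistent with the early-transfer power, is the largest limit the protocol can support. A smaller one is needed if a 6-point excess is regarded as relevant harm.
3. Leave transfer back to hospital out of the between-group count, since only home patients can have it, and report it descriptively.
4. Conclude that safety is maintained only if the upper limit of the two-sided 95% confidence interval for the propensity-weighted difference is below the margin. Otherwise report the estimate and interval as inconclusive.

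Cost: an entry in the endpoint table, a short methods paragraph and the justification of a margin. No new patients or data are needed. The downside is that with a small control group the safety result may have to be reported as inconclusive.

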## SUBJECT SELECTION

### Inclusion/exclusion criteria

#### *Inclusion*

- Social
  - Resides within either a 7.5-mile driving radius of the BWFH emergency room
    - Driving radius will be obtained via inputting a nearby (but not exact) address into Google Maps.
  - Has capacity to consent to study OR can assent to study and has proxy who can consent (see subject enrollment, below)
  - Can identify a potential caregiver who agrees to stay with patient for first 24 hours of admission. Caregiver must be competent to call care team if a problem is evident to her/him. After 24 hours, this caregiver should be available for as-needed spot checks on the patient.
    - This criterion may be waived for highly competent patients at the patient and clinician's discretion.
- Clinical
  - $\geq 18$  years old
  - Primary or possible diagnosis of cellulitis, heart failure, complicated urinary tract infection, pneumonia, COPD/asthma, other infection, chronic kidney disease, malignant pain, diabetes and its complications, gout flare, hypertensive urgency, previously diagnosed atrial fibrillation with rapid ventricular response, anticoagulation needs, or a patient who desires only medical management that requires inpatient admission, as determined by the emergency room team.
    - Regarding anticoagulation needs, this includes a patient who requires therapeutic anticoagulation and concomitant monitoring (thus requiring inpatient status)
    - Regarding a patient who desires only medical management, this includes a patient who requires acute care for symptom management, but declines any surgical intervention. This may include a patient who is about to transition to hospice care, for example, but still has the functional capacity to meet our criteria below. Under these circumstances, we would make sure that various contingencies, including possible transition to hospice care or hospital readmission, are completely understood by patients and caregivers as applicable.
    - In order to achieve enrollment goals, we *a priori* reserve the ability to expand this criterion to include patients who fail observation status and patients who

are transferred to the observation unit under the care of the emergency room observation team.

- Regarding IBD
  - Requires intravenous infusion and acute care monitoring per outpatient gastroenterologist
- Regarding acute pancreatitis
  - Please refer to attachment
- Regarding exacerbation of cystic fibrosis or non-cystic fibrosis bronchiectasis
  - Exacerbation ( $\geq 4/12$ )
    - Change in sputum
    - New or increased hemoptysis
    - Increased cough
    - Increased dyspnea
    - Malaise, fatigue or lethargy
    - Temperature above 38°C
    - Anorexia or weight loss
    - Sinus pain or tenderness
    - Change in sinus discharge
    - Change in physical examination of the chest;
    - Decrease in pulmonary function by 10 percent or more from a previously recorded value
    - Radiographic changes indicative of pulmonary infection
- Location of presentation
  - Emergency department
    - Decision to admit or observe patient made by emergency department
  - Hospital floor
    - Patient is clinically stable with a clear plan for continued acute care, as agreed upon by the inpatient and home hospital teams
    - All inclusion and exclusion criteria must still be fulfilled
  - Home
    - Patient is known to the home hospital team from a prior home hospitalization
    - All inclusion and exclusion criteria must still be fulfilled. This requires the same clinically warranted workup as the patient would have received in the emergency department or upon arrival to the floor, including imaging and other diagnostics. Should these be warranted and not be available (e.g., expedited CT imaging), the patient would be excluded.
  - Clinic
    - Patient is well-known by a referring clinician who is confident of the diagnosis and management after a history, physical, and if warranted diagnostic testing in the clinic. For example, a cardiologist might refer a patient with known heart failure from clinic who has volume overload and would otherwise directly admit her/his patient to the floor.
    - All inclusion and exclusion criteria must still be fulfilled. This requires the same clinically warranted workup as the patient would have received in the emergency department or upon arrival to the floor, including imaging and other diagnostics. Should these be warranted and not be available (e.g., expedited formal TTE), the patient would be excluded.

*Exclusion*

- Social
  - Undomiciled
  - No working heat (October-April), no working air conditioning if forecast > 80°F (June-September), or no running water
  - On methadone requiring daily pickup of medication
  - In police custody
  - Resides in facility that provides on-site medical care (e.g., skilled nursing facility)
  - Domestic violence screen positive
- Clinical
  - Acute delirium, as determined by the Confusion Assessment Method
  - Cannot establish peripheral access in emergency department (or access requires ultrasound guidance, unless point-of-care ultrasound is available)
  - Secondary condition: end-stage renal disease on hemodialysis, acute myocardial infarction, acute cerebral vascular accident, acute hemorrhage
  - Primary diagnosis requires multiple or routine administrations of intravenous narcotics for pain control
  - Cannot independently ambulate to bedside commode, unless home-based aides are available
  - As deemed by on-call MD, patient likely to require any of the following procedures: computed tomography, magnetic resonance imaging, endoscopic procedure, blood transfusion, cardiac stress test, or surgery (unless expedited pathway for these procedures is available)
  - For pneumonia:
    - Most recent CURB65 > 3: new confusion, BUN > 19mg/dL, respiratory rate ≥ 30/min, systolic blood pressure < 90mmHg, Age ≥ 65 (<14% 30-day mortality)
    - Most recent SMARTCO > 2: systolic blood pressure < 90mmHg (2pts), multilobar CXR involvement (1pt), respiratory rate ≥ 30/min, heart rate ≥ 125, new confusion, oxygen saturation ≤ 90% (<10% chance of intensive respiratory or vasopressor support)
    - Absence of clear infiltrate on imaging
    - Cavitory lesion on imaging
    - Pulmonary effusion of unknown etiology
    - O2 saturation < 90% despite 5L O2
  - For heart failure:
    - Has a left ventricular assist device
    - GWTH-HF (>10% in-hospital mortality) or ADHERE (high risk or intermediate risk 1)\*
    - Severe pulmonary hypertension
  - For complicated urinary tract infection:
    - Absence of pyuria
    - Most recent qSOFA > 1 (SBP ≤ 100 mmHg, RR ≥ 22, GCS < 15 [any AMS]) (if sepsis, >10% mortality)
  - For other infection
    - Most recent qSOFA > 1 (SBP ≤ 100 mmHg, RR ≥ 22, GCS < 15 [any AMS]) (if sepsis, >10% mortality)
  - For COPD

- BAP-65 score > 3 (BUN>25, altered mental status, HR>109, age>65) (<13% chance in-hospital mortality): exercise caution
- For asthma
  - Peak expiratory flow < 50% of normal: exercise caution
- For diabetes and its complications
  - Requires IV insulin
- For hypertensive urgency
  - Systolic blood pressure > 190 mmHg
  - Evidence of end-organ damage; for example, acute kidney injury, focal neurologic deficits, myocardial infarction
- For atrial fibrillation with rapid ventricular response
  - Likely to require cardioversion
  - New atrial fibrillation with rapid ventricular response
  - Unstable blood pressure, respiratory rate, or oxygenation
  - Despite IV beta and/or calcium channel blockade in the emergency department, HR remains > 125 and SBP remains different than baseline
  - Less than 1 hour of time has elapsed with HR < 125 and SBP similar or higher than baseline
- For patients with end-stage renal disease on peritoneal dialysis
  - Peritoneal catheter malfunction
  - Requires temporary hemodialysis
- For exacerbation of IBD
  - Fever > 102F
  - Rigid/surgical abdomen
  - Acute intestinal obstruction, perforation, or toxic megacolon
  - History of intestinal obstruction, perforation, toxic megacolon
  - Abscess or abdominal mass
  - Likely to require total parenteral nutrition
  - Likely to require blood transfusion
- For acute pancreatitis
  - Please refer to attachment
- For exacerbation of cystic fibrosis or non-cystic fibrosis bronchiectasis
  - Pneumonia criteria above
  - Respiratory failure
  - Moderate or large-volume hemoptysis ( $\geq 10\text{mL}$ )
  - Pneumothorax
  - Pancreatitis
  - Post-transplant
- Home hospital census is full (maximum 16 patients at any time)

\*GWTG-HF: AHA Get with the Guidelines: SBP, BUN, Na, Age, HR, Black race, COPD  
 ADHERE: Acute decompensated heart failure national registry: BUN, creatinine, SBP

